### Outcome measurements

#### Primary outcome

The primary outcome will be measured via a questionnaire that confirms subjective symptom improvement. Participants will respond a total of five times during and after the administration period (at 2 and 6 weeks via telephone, and at 4, 8 and 12 weeks during direct visits) to the following question: Subject’s Global Assessment of Relief—‘How much do you think the symptoms of D-IBS have improved compared to before the clinical trial?’ According to the answers given by the patients to this survey, the improvement is given a score of 0, 1, 2, 3 or 4.

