#### Statistical analysis

The statistical analysis will be conducted by blinded professional statisticians. To evaluate the efficacy of the study, both an intent-to-treat (ITT) analysis (primary analytical method) and a per-protocol (PP) analysis (secondary analytical method) will be performed. The ITT analysis will be conducted for all patients who were followed up at least once after randomisation and will be able to be evaluated for effectiveness. The PP analysis will be performed for patients who complete the 8-week treatment course and meet the inclusion and exclusion criteria.

To analyse the continuous variables in the demographic information and pretreatment characteristics between groups, a one-way analysis of variance (ANOVA) and Kruskal-Wallis test will be conducted. An ANOVA and Kruskal-Wallis test will also be used to test for symptom improvement compared with baseline (0 week) and the variables for analysis that include the following: (1) subjective symptom improvement (primary outcomes) and (2) severity of symptoms related to D-IBS (abdominal pain, abdominal discomfort, satisfaction of defecation, frequency of abdominal pain and quality of life). All values will be shown as mean±SEM. Comparisons of outcome assessments between the four groups will be performed using the paired t-test or Wilcoxon signed-rank test.

If the Subject’s Global Assessment of Relief on the Likert scale is ‘0’ or ‘1’ for more than 2 weeks between weeks 8 and 12, then the symptoms will be considered to have improved sufficiently. Based on this, we will calculate the symptom relief rate by dividing the number of participants who exhibited sufficient symptom relief by the total number of participants in the trial and present descriptive statistics. The CATMOD procedure will be used to evaluate the improvement of symptoms compared with baseline. Comparisons between the four groups will be conducted using the χ^2^ test or Fisher’s exact test. These statistical analyses will also be performed at 2, 4, 6, 8 and 10 weeks from baseline. The Cochran-Mantel-Haenszel test will be used to confirm the difference between the intervention groups at each time point.

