A statistical analysis will also be conducted to evaluate safety. The incidence of adverse events and abnormality of experimental results will be analysed statistically according to the groups, and non-parametric methods will be applied as necessary using a paired t-test for continuous data, McNemar’s test for categorical data, Fisher’s exact test for adverse events and a generalised estimating equation for clinically significant changes between groups.

All statistical analyses will be conducted using SAS software, V.9.1.3 (SAS institute). A P value <0.05 will be considered statistically significant.

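### The primary relief item is tested both as a 0–4 score and as a relief rate, each at P<0.05, and the protocol does not say which one decides efficacy

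*Protocol article*

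**What the plan says.** **The outcome.** The Abstract and the Primary outcome section name one primary outcome, the Subject's Global Assessment of Relief. It is asked at weeks 2, 4, 6, 8 and 12, and "the improvement is given a score of 0, 1, 2, 3 or 4".

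**Form 1, the score.** In Statistical analysis: "An ANOVA and Kruskal-Wallis test will also be used to test for symptom improvement compared with baseline (0 week"). The first variable listed for this is "1) subjective symptom improvement (primary outcomes"); the secondary severity items follow in the same list. The paragraph ends by naming the paired t-test or Wilcoxon signed-rank test for comparing outcomes between the four groups.

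**Form 2, the rate.** The next paragraph takes a score of 0 or 1 "for more than 2 weeks between weeks 8 and 12, then the symptoms will be considered to have improved sufficiently". From this, "we will calculate the symptom relief rate by dividing the number of participants who exhibited sufficient symptom relief by the total number of participants", with descriptive statistics. Testing follows: "Comparisons between the four groups will be conducted using the" χ² or Fisher's exact test, CATMOD for change from baseline, and Cochran-Mantel-Haenszel (CMH) for group differences at each time point. Also: "These statistical analyses will also be performed at 2, 4, 6, 8 and 10 weeks from baseline".

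**The level.** One rule covers everything: "A P value <0.05 will be considered statistically significant".

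**Related text.** The second hypothesis places the comparison with placebo after 8 weeks of treatment. The Statistical analysis section ranks intention-to-treat as primary and per-protocol as secondary. It does not rank the two forms of the outcome.

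**The concern.** A mean or rank comparison of a 0–4 score and a comparison of the proportion scoring 0 or 1 are different endpoints, although they come from the same answers. The score carries the primary label, while the only definition of sufficient improvement belongs to the rate. With arms this small, the two will often differ in significance. A report could then present whichever form reached P<0.05 as the primary result without departing from the text, and the 5% level would not hold for the efficacy claim.

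The point concerns the form of the endpoint and its test at one evaluation. Repetition over visits and the wording of the responder window are separate matters.

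**Working it through.** **Inputs from the protocol.** Four arms of 20; 16 completers per arm; 20% dropout; a 0–4 score; responder = score 0 or 1; P<0.05 for every test.

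**The plan's own figure.** 16 / (1 − 0.20) = 20 per arm, and 4 × 20 = 80. This reproduces the stated size. It involves no power, effect size or error rate, so the plan has no error figure to reproduce.

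**Reference value.** Two independent tests at 0.05 give 1 − 0.95² = 9.75%. The two forms share data and are positively related, so the real figure should be lower.

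**Simulation under no treatment effect.** Assumptions, none of them in the protocol: a latent normal variable cut to 0–4 under several distributions, 16 or 20 per arm, and a range of week-8/week-12 correlations, with 20,000–40,000 replicates per setting. The responder window can be read in two ways, so both were run.

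| Null hypothesis, four arms | Either form significant |
|---|---|
| Week-8 score (ANOVA or Kruskal-Wallis), rate from the same visit | 7.0–8.6% |
| Week-8 score, responder at both weeks 8 and 12 | 7.2–9.4% |
| Week-8 ANOVA or Kruskal-Wallis, or the two-visit rate | 8.3–9.5% |

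The score test alone, or the same-visit rate alone, gives 4.5–5.3%.

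**One null setting in full.** 20 per arm, score probabilities 10/25/30/25/10%:
- Same visit: Kruskal-Wallis 4.77%, χ² 4.89%, either 7.36%. Both: 4.77 + 4.89 − 7.36 = 2.30%. Exactly one: 7.36 − 2.30 = 5.06%.
- Two-visit responder, correlation 0.5: 4.74%, 4.78%, either 8.58%. Both: 4.74 + 4.78 − 8.58 = 0.94%. Exactly one: 8.58 − 0.94 = 7.64%.

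**Disagreement under a treatment effect.** Assumed latent benefit of 0.8 SD for the combination and 0.4 SD for each single drug, 20 per arm, same-visit rate: Kruskal-Wallis 45.7%, χ² 33.9%, either 49.3%.
- Both: 45.7 + 33.9 − 49.3 = 30.3%.
- Exactly one: 49.3 − 30.3 = 19.0%.
- Score only: 49.3 − 33.9 = 15.4%. Rate only: 49.3 − 45.7 = 3.6%.

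Across the effect patterns and distributions tried, exactly one form was significant in about 15–25% of trials with the same-visit rate and about 21–37% with the two-visit responder. Overall this is roughly 15–35%.

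**The case against.** The strongest reply is that the protocol already points to the score. The primary outcome is defined only as the 0–4 item, the primary label stands beside the score and nowhere beside the rate, the rate is introduced descriptively, and the second hypothesis fixes 8 weeks. All of this stands, so a reader who infers that the protocol gives no indication at all goes too far. It still falls short of a rule. The label sits in a list of variables that also includes secondary items, and the rate is then compared between arms by inferential tests under the same 5% level.

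A second reply is that the full analysis plan may settle the matter. Ordinary detail can be left there. Here, however, the article itself fixes both forms, their tests and the level without an order between them.

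A third reply is that ANOVA and Kruskal-Wallis may be shorthand for choosing by distribution, since the same section uses the word or for its other pairs of tests. That is possible, though the text says and. It matters little: adding the second score test moves the error rate by only about half a percentage point.

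Finally, repetition over visits inflates error more. Counting any significant result from both forms at five visits gives 19–28% in the assumed model. That is a separate problem, and naming a visit would not cure this one.

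**Conclusion.** The point holds as an unranked pair of tests on the primary outcome. The article leans towards the week-8 score but never says that it decides, or that the relief rate is supportive. If either form may count, the false-positive rate at one evaluation is about 7–9% instead of 5%. It exceeded 5% in every setting tried. The size depends on assumed score distributions and between-visit correlations.

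Two stronger readings are not supported:
- A flat rate of about 9% is the top of the range. It needs the two-visit responder reading and, in most settings, a moderate or weak correlation between visits. The same-visit reading, which the by-week analyses allow, gives 7.0–8.6%.
- The two forms do not give opposite verdicts in the sense of favouring different arms. The calculations show only that one can be significant and the other not, in roughly 15–35% of trials under moderate assumed effects.

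**What to change.** In the Statistical analysis section, state that efficacy is decided by the 0–4 relief score at week 8, compared between arms by one test at 0.05: Kruskal-Wallis or an equivalent rank or ordinal model. For the primary outcome, that test should replace two sentences: the one naming ANOVA and Kruskal-Wallis, and the one naming the paired t-test or Wilcoxon signed-rank test for comparisons between the four groups. If the second sentence stays, a further between-group test of the same score remains in the plan. Label the relief rate and its χ²/Fisher, CATMOD and CMH analyses as supportive.

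This takes a sentence or two and no new data. The cost is that a significant relief rate alone can no longer be reported as a positive primary result. In the same-visit example above, that gives up 3.6 percentage points of trials. With the two-visit responder at 20 per arm (ANOVA 48%, rate 36–41%, disagreement 27–33%), the share significant on the rate only is (36 + 27 − 48)/2 = 7.5 to (41 + 33 − 48)/2 = 13 points. Those extra positives are available only at the raised error rate. In these runs the score test had more power than the rate, so the proposed choice also keeps the stronger form.

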Otilonium bromide (OB) is widely used for the prevention and reduction of symptoms in patients with IBS.^7 8^ OB has been shown to inhibit L-type and T-type calcium channels, muscarinic receptors and tachykininergic responses in human cultured smooth muscle cells and rat colon strips.^19–21^ According to a recent randomised controlled trial (RCT), OB (40 and 80 mg) is more effective for treating IBS than placebo, not only for the reduction of bloating and abdominal pain but also for protection from relapse owing to its long-lasting effect.^22 23^

According to the guidelines of the Korean Society of Gastroenterology, antispasmodic agents are recommended for the treatment of D-IBS (grade 1B),^24^ and SRS is the preferred drug for diarrhoea treatment in Korean medicine.^18^ Recently, several studies have been conducted to evaluate the therapeutic effect of the coadministration of herbal formulae and conventional drugs for IBS in China.^25 26^ However, there has been no such clinical study in Korea, even though both herbal medicine and conventional drugs are widely used for IBS treatment in the clinical field. Therefore, there is a need to evaluate the efficacy and safety of SRS, OB and the coadministration of both drugs.

In this study, we expect that the combined administration of OB and SRS will result in synergistic effects that improve D-IBS symptoms, including abdominal pain, discomfort (the main effect of OB) and diarrhoea-like stool patterns (the main effect of SRS).

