### Hypothesis

We hypothesise: (1) that coadministration of SRS and OB will have a more positive effect on D-IBS symptoms than either SRS or OB alone; (2) that after 8 weeks of treatment with SRS, OB or both drugs, the Subject’s Global Assessment of Relief and severity of D-IBS symptoms will be more improved than after treatment with placebo and (3) that coadministration of SRS and OB will be safe for patients with D-IBS.

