### Sample size calculation

This trial is a study for a new therapeutic regimen of SRS and OB combination treatment. In a similar study conducted previously by using coadministration of a probiotics mixture and an herbal medicine (placebo-controlled, double-blind and randomly four-arm trial), each arm consisted of at least 15 patients, and the total sample size was more than 60 participants.^27^ In other similar studies, clinical trials have been conducted with a total of 60–64 participants, consisting of 12–30 patients per group.^28–30^ Based on these previous studies, the minimal clinical significance of the trial can be obtained when only 16 participants complete the trial. Because the dropout rate is expected to be 20%, each trial group will be made up of at least 20 participants. Therefore, the total sample size must be more than 80 participants.

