Because only a few studies have evaluated the combination of herbal and conventional drugs, our proposed study will significantly contribute to overcoming the limitations of previous studies and provide basic medical evidence for the coadministration of SRS and OB for D-IBS treatment. Therefore, this RCT has several characteristic features. First, this trial will be the first to investigate the efficacy of SRS and OB combination therapy for D-IBS. The results of previous studies suggested that the combination of OB and SRS will improve two major D-IBS symptoms at the same time: abdominal pain and discomfort (major effect of OB) and diarrhoea (main effect of SRS). This study will assess this hypothesis and provide a basis for the use of SRS and OB combination therapy for D-IBS. Second, the participants in this trial will be grouped into four arms, making it possible to compare the efficacy of combined treatment with the efficacy of each individual treatment. Third, this trial will evaluate the safety of the subjects using several assessments, including a periodic assessment of subjective symptoms, physical measurements and laboratory testing. The results of the safety analysis may provide evidence for the safety of treatment with the combination of herbal and conventional drugs in D-IBS. Fourth, this trial was the first clinical study related to combination treatment with Western and traditional herbal medicine in Korea to receive approval from the KMFDS. Through the systematic management of the trial under the auspices of the KMFDS, a high-quality trial will be performed, and the results of this study will provide information for use in further clinical applications.

Although our trial is designed with a small sample size, it has a creative and systematic research design, and the results will be useful basic clinical evidence in the field of integrated herbal and conventional drugs for the management of D-IBS.

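### No named efficacy test addresses the first hypothesis (combination better than each drug alone), the four-group tests are repeated at five times at P<0.05, and 16 completers per arm is unsupported

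*Protocol article*

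**What the plan says.** **Question.** Hypothesis 1 in the Hypothesis section is "that coadministration of SRS and OB will have a more positive effect on D-IBS symptoms than either SRS or OB alone". Hypothesis 2 compares the active arms with placebo: "that after 8 weeks of treatment with SRS, OB or both drugs". The Discussion gives the reason for four arms as "making it possible to compare the efficacy of combined treatment with the efficacy of each individual treatment". The Introduction adds an expectation: "the combined administration of OB and SRS will result in synergistic effects that improve D-IBS symptoms".

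**Analysis.** The Statistical analysis section names these efficacy tests:
- ANOVA and Kruskal-Wallis for the relief score and the symptom severity scores;
- a paired t-test or Wilcoxon signed-rank test for comparing the four groups;
- the CATMOD procedure for change from baseline in the relief rate;
- χ² or Fisher's exact test across the four groups for the relief rate;
- a further between-group test: "The Cochran-Mantel-Haenszel test will be used to confirm the difference between the intervention groups at each time point".

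The analyses are repeated at five times. The threshold is common to all of them: "A P value <0.05 will be considered statistically significant".

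**Size.** The Sample size calculation section cites the numbers enrolled in similar trials and concludes that "the minimal clinical significance of the trial can be obtained when only 16 participants complete the trial". It then allows for 20% dropout.

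**The concern.** The four arms form a complete 2×2 layout (SRS yes or no, OB yes or no). Hypothesis 1 needs two directed comparisons, combination v SRS alone and combination v OB alone, and both must favour the combination. A four-group test asks only whether the four arms are not all alike. It can be significant because one drug beats placebo while the other contributes nothing. Read as support for coadministration, such a result would answer the wrong question.

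Two further features weaken the reading of any result. The primary outcome is analysed both as a 0–4 score and as a relief rate, at five times, each at 0.05, so there are many routes to a positive finding. The size statement also gives no effect size, SD, response rate or power, so a reader cannot tell what a null result would exclude.

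**Working it through.** **1. The plan's own size figure.** Inputs from the Sample size calculation section: 16 completers, 20% dropout. 16 / (1 − 0.20) = 20 per arm, and 4 × 20 = 80. The dropout step is correct. The 16 cannot be derived, because no effect size, SD, rate or power is given.

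**2. Hypotheses against named tests.**

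| Needed | Named in Statistical analysis |
|---|---|
| Combination v SRS; combination v OB | No such contrast; CMH sentence specifies no arms |
| Each active arm v placebo, after 8 weeks | No such contrast; no primary time point |
| SRS-by-OB term, if synergy is to be claimed | Not named |
| Test for independent arms | Paired t or signed-rank assigned to the four-group comparison; these are within-subject tests |

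**3. What a significant four-group test would mean.** Assume OB shifts the outcome by 0.8 SD and SRS does nothing. Means in SD units: placebo 0, SRS 0, OB 0.8, combination 0.8; overall mean 0.4. The noncentrality is λ = n Σ(μᵢ − μ̄)² = n × 4 × 0.4² = 0.64n.
- 16 per arm: λ = 10.24, F on 3 and 60 df, power 74%.
- 20 per arm: λ = 12.8, F on 3 and 76 df, power 85%.

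If instead all three active arms are 0.8 SD better than placebo and the combination adds nothing, the figures are 60% and 72%. By contrast, the requirement that the combination beat OB at two-sided 0.05 would be met falsely, in the favourable direction, at most 0.05 / 2 = 2.5% of the time in the first scenario.

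**4. Repeated testing with no effect at all.** Five independent tests at 0.05 give 1 − 0.95⁵ = 22.6%. Visits are correlated, so this was simulated with 20 per arm, a five-level score, 40% of patients in the two categories that count as relief, and assumed between-visit correlation of 0.8 down to 0.4:
- ANOVA alone over five visits: at least one P<0.05 in about 15–20% of trials;
- with Kruskal-Wallis and χ² on the relief rate added: about 22–31%.

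**5. What 16 or 20 per arm can detect.** For one pairwise comparison the standard error is SD × √(2/n), that is 0.354 SD at 16 and 0.316 SD at 20. With the noncentral t, two-sided 0.05 and 80% power, the detectable difference is 1.02 SD at 16 per arm and 0.91 SD at 20 per arm. For the SRS-by-OB interaction the standard error is 2 SD/√n, and the figures are 1.42 and 1.27 SD. For relief rates at 16 per arm, exact Fisher power is about 50% for 40% v 80% and 79% for 40% v 90%.

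**6. Chance of winning both combination contrasts.** If the combination is 0.5 SD better than each single drug (assumed), both contrasts succeed in about 14% of trials at 16 per arm and 19% at 20 per arm (15% and 20% with a variance pooled over all four arms).

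**The case against.** The article condenses a fuller protocol, and a SAP that is not shown may name contrasts, a primary time point and a multiplicity rule. The CMH sentence does not say whether it is global or pairwise, and hypothesis 2 does point to week 8. A reader might therefore go too far in inferring that the hypotheses are never tested. What can be said is that no named test addresses hypothesis 1. That stands, because the article sets out its tests at length and those it describes clearly answer another question or, for the paired tests, cannot be applied to independent arms.

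A reader might also infer that synergy is one of the trial's hypotheses and that the missing interaction test is a failure against it. The Hypothesis section lists three hypotheses and synergy is not among them. It is an expectation in the Introduction, where it seems to mean complementary action on pain and on diarrhoea. The interaction matters only if synergy is to be claimed.

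It is equally tempting to say that 16 per arm fails to deliver what is claimed. The document sets no target effect or power to miss, and both the strengths-and-limitations list and the Discussion concede a small sample. The supportable criticism is that the sentence has no basis. Finally, false-positive counts that include all pairwise comparisons should not be charged to a plan that does not name them, so they are left out here.

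**Conclusion.** The point holds as a mismatch within the stated text. The trial's first question is combination v each single drug, and no efficacy test named in the article is directed at it. Followed as written, the four-group F test would be significant in about 74–85% of trials in which SRS adds nothing to an effective OB. Unadjusted repetition over five visits raises the chance of a false positive to about 15–20% for ANOVA alone and about 22–31% for the wider set of named tests. The statement about 16 completers is unsupported; at that size a pairwise comparison reaches 80% power only for a difference of about 1 SD.

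These figures rest on assumed effect sizes (0.8 and 0.5 SD), assumed visit correlations (0.4–0.8), an assumed 40% relief rate and a two-sided 0.05, since the article does not state sidedness. The mismatch itself needs no assumption.

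**What to change.** - Make the relief score at week 8 the primary analysis, in a model with SRS, OB and SRS-by-OB terms. Replace the paired tests between arms with between-group contrasts from that model.
- Count hypothesis 1 as supported only if combination v SRS and combination v OB both favour the combination at two-sided 0.05. Because both must succeed, no split of alpha is needed.
- For hypothesis 2, test each active arm v placebo, either in a fixed order named in advance after hypothesis 1 has succeeded, or labelled supportive.
- Report the interaction with a 95% CI as descriptive, and make no claim of synergy without it.
- Label the relief rate, the other visits and the other tests supportive.
- Replace the sentence on 16 completers with the detectable differences (80% power, pairwise: 1.02 SD at 16 per arm, 0.91 SD at 20 per arm) and call the trial exploratory, in line with its own stated limitation.

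The cost is protocol and SAP wording, with no extra patients; recruitment was ongoing at the time of the article, and the change should be made before unblinding. The downside is that the combination claim becomes harder to win, at about 14–19% if the true gain over each drug is 0.5 SD, and that the size statement reads less favourably.

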**Trial registration number:**

KCT0001621 (approval date: 10 August 2015).

Strengths and limitations of this studyThis randomised controlled trial is the first Korean clinical trial approved by the Korean Ministry of Food and Drug Safety to investigate the efficacy and safety of Samryungbaekchulsan (SRS; herbal formula) and otilonium bromide (OB; Western drug) in diarrhoea-predominant irritable bowel syndrome (D-IBS).To evaluate the therapeutic effect and safety of the coadministration of SRS and OB, this study is proposed as a double-blind, double-dummy, four-arm, parallel-group randomised controlled trial.The primary outcome is the improvement in the patient’s symptoms according to the Subject’s Global Assessment of Relief, and the secondary outcome is the severity of D-IBS symptoms.This study is conducted with a small sample size (four arms, 20 participants per group), so further clinical trials with powerful sample sizes will be required to more adequately determine the effectiveness of SRS and/or OB in D-IBS.

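### The safety hypothesis asserts that the combination will be safe, but the only test named for adverse events is a difference test with 20 per arm, which cannot show that harm is absent

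*Protocol article*

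**What the plan says.** All references are to the protocol article.

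- **Hypothesis**, third item: "that coadministration of SRS and OB will be safe for patients with D-IBS". Objectives also makes safety part of the trial's purpose.
- **Statistical analysis**, safety paragraph: "non-parametric methods will be applied as necessary using a paired t-test for continuous data, McNemar’s test for categorical data", followed by "Fisher’s exact test for adverse events and a generalised estimating equation for clinically significant changes between groups". The threshold for all analyses is "A P value <0.05 will be considered statistically significant".
- **Sample size calculation**: "each trial group will be made up of at least 20 participants". The number comes from the size of earlier trials, with no event rate and no power.
- **Discussion**: "The results of the safety analysis may provide evidence for the safety of treatment with the combination of herbal and conventional drugs in D-IBS".
- **Strengths and limitations of this study**: the small-sample caveat says that "further clinical trials with powerful sample sizes will be required to more adequately determine the effectiveness of SRS and/or OB in D-IBS". It names effectiveness and not safety.
- **Safety assessments** and **Laboratory tests**: the investigator records severity and causality for each event and judges which reactions the drugs caused. Detailed statistics on laboratory data are ruled out because the sample is small.

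**The concern.** A hypothesis that a treatment is safe is a claim that any excess harm is absent or tolerably small. Data support such a claim when an upper bound on the excess lies below some acceptable level. The article states no acceptable level and no bound. The method it does name asks the opposite question: whether there is enough evidence to declare a difference. A non-significant answer leaves both no harm and considerable harm open, and the smaller the arms, the easier it is to obtain.

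The conclusion on coadministration is at stake. The article itself says that guidance on combining herbal and conventional drugs is lacking, so readers may lean on whatever the trial says about safety.

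**Working it through.** **Inputs.** 20 randomised per arm and 16 completers with 20% dropout (Sample size calculation); Fisher's exact test and P<0.05 (Statistical analysis). Sidedness is not stated, so two-sided is assumed. Adverse-event rates are not given, so a range is assumed.

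**1. The plan's own figure.** 16 / (1 - 0.20) = 20 per arm, and 4 x 20 = 80. It reproduces, but it has no link to any safety question.

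**2. Power to detect a tripled event rate, 20 versus 20.** With X ~ Bin(20, p) and Y ~ Bin(20, 3p), power is the sum of P(X=i) x P(Y=j) over all pairs (i, j) for which the two-sided Fisher P is below 0.05.

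| Assumed baseline p | 3p | Power, pairwise two-sided |
|---|---|---|
| 5% | 15% | 7% |
| 10% | 30% | 24% |
| 15% | 45% | 44% |
| 17% | 51% | 53% |
| 20% | 60% | 65% |
| 25% | 75% | 83% |

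Power crosses 50% at a baseline of about 17%.

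**3. Other forms of the comparison**, at baselines of 5%, 10%, 15% and 20%, with one arm tripled:

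- one-sided pairwise: 9%, 34%, 57%, 75%
- four-arm exact test (4,000 simulated trials): about 11%, 33%, 56%, 79%
- combination against the other three arms pooled (20 versus 60): 27%, 50%, 72%, 88%

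These are somewhat better, but power is still at or below 50% at baselines of 5% and 10%.

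**4. Smallest significant results, 20 versus 20.** 0 v 5 (P=0.047), 1 v 7 (P=0.044), 2 v 9 (P=0.031), 3 v 10 (P=0.041). Observed triplings of 1 v 3 (P=0.60), 2 v 6 (P=0.24) and 3 v 9 (P=0.08) are all non-significant.

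**5. What a non-significant result leaves open.** Take 6/20 on the combination and 2/20 on the comparator. The difference is 0.30 - 0.10 = 0.20. The Wilson 95% limits are 0.145 to 0.519 and 0.028 to 0.301. Newcombe's interval is:

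- lower: 0.20 - sqrt[(0.300 - 0.145)² + (0.301 - 0.100)²] = -0.05
- upper: 0.20 + sqrt[(0.519 - 0.300)² + (0.100 - 0.028)²] = +0.43

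So P=0.24 goes with an excess anywhere from -5 to +43 percentage points.

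**6. Best case, no events on the combination.** The exact two-sided 95% upper limit for 0/20 is 1 - 0.025^(1/20) = 0.168, or 16.8%.

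**The case against.** Several stronger readings are tempting, and the article does not support them.

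- **That a non-significant test will be reported as safe.** A reader might infer this from the hypothesis and the named test. No section says it, and the Discussion is hedged: the results only may provide evidence.
- **That Fisher's test is the sole criterion for safety.** No test is made a criterion. A paired t-test, McNemar's test and a generalised estimating equation are also named, and the investigator judges causality event by event. However, the first two compare patients with themselves, the third again looks for differences, and individual causality judgement does not bound the excess risk between arms. Fisher's is the only test named for adverse events.
- **That a tripled rate would usually be missed.** This depends on an unknown baseline. It holds pairwise up to about 15% and reverses from about 17%; for the four-arm test it has already reversed at 15%.
- **That nothing in the article restrains safety inference.** Laboratory tests does so for laboratory data, and the Discussion closes with a general remark on the small sample. Neither limits the adverse-event comparison, and the caveat under Strengths and limitations names effectiveness only.
- **That the calculation should use the 16 completers.** All adverse events during the trial are recorded, so the 20 randomised are the fitting denominator.

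It is also fair to say that Fisher's test is a reasonable choice for sparse events, and that interval methods and event categories are usually left to the full protocol or SAP, which are not shown. Their absence is therefore not the point. The point is the mismatch between a hypothesis and a test that the article does state. An SAP could add intervals, but it would not by itself change the wording of the hypothesis.

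**Conclusion.** The concern holds in limited form. The stated adverse-event analysis cannot support the stated safety hypothesis, because a difference test without a margin or interval does not establish the absence of harm. That conclusion is one of logic and needs no assumed rate.

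Its practical size does rest on assumptions: two-sided 5%, a pairwise comparison of 20 versus 20, and baseline rates that the article does not give. At baselines of 15% or below, a tripling is more likely to be missed than found. At 20% or above it is more likely to be found. Even the most favourable result on the combination arm, no events in 20, does not exclude a true rate of up to about 17%. Nothing here shows that the combination is harmful or that the results will be misreported.

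**What to change.** 1. **Statistical analysis.** Base the adverse-event conclusion on estimates in all treated patients: the risk in each arm, and the risk difference for the combination minus placebo and minus each single drug, each with a 95% confidence interval. Keep Fisher's P value as supportive, and state that P>0.05 is not evidence of safety. Say that the interval leads, because at these sizes the two can disagree: 3/20 versus 9/20 gives P=0.08 but a Newcombe interval of about +2 to +53 points.
2. **Hypothesis.** Reword the third item as describing the tolerability of coadministration, reported with the upper 95% limit of the excess adverse-event risk.
3. **Strengths and limitations of this study.** Extend the small-sample caveat from effectiveness to safety.

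The cost is wording plus a few intervals from data already collected, with no extra patients or procedures. The small downside is that the trial gives up an unqualified claim of safety and reports a wide interval instead.
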